#### Exploratory analyses

To analyse data collected at multiple regular intervals before and after the intervention, an ITS analysis will be performed. A linear regression model will be estimated as follows:

$$\begin{array}{l} Y=b_{0}+b_{1}T+b_{2}I+e \end{array}$$

where:

Y: outcome variable (CMDD-M score, prevalence of patients achieving the maximum score on CMDD-M, PIMCH-Q score or the number of non-adherence instances to medication changes persisting post-discharge)

b_0_: intercept, representing the expected value of the outcome variable (Y) at baseline (T=0 and I=0).

b_1_: time effect, indicating the change of the outcome variable (Y) for each day passed, regardless of the intervention.

T: time in days passed from the start of the study, capturing natural changes in the outcome over time.

b_2_: intervention effect, representing the difference in the outcome variable (Y) between pre-intervention (I=0) and post-intervention (I=1) periods, after accounting for time trends.

I: dummy variable indicating whether the observation was collected before (0) or after (1) intervention, enabling comparison outcomes before and after the intervention.

e: error term, capturing random noise or unexplained variation in the outcome variable (Y).

This model will allow us to investigate whether there is an immediate effect following the intervention. Results will be presented as regression estimates with 95% CI and p values. This analysis will be conducted for the following outcomes: CMDD-M score, prevalence of patients achieving the maximum score on CMDD-M, PIMCH-Q score (the three dimensions separately and total score), the number of non-adherence instances to medication changes persisting post-discharge and prevalence of patients who are fully adherent to medication changes.

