#### Rationale for study design

A randomised trial was deemed infeasible—neither at the patient level, due to contamination risks, nor at the ward level or as a stepped-wedge design, as these would require a large number of wards and exceed available resources. Consequently, a pre–post study design was selected, complemented by an interrupted time series (ITS) analysis for exploratory purposes. The ITS analysis, analysing data at regular intervals both before and after the intervention, allows for a more nuanced interpretation of the primary results by accounting for potential seasonal variations and changes in effect over time.

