### Statistical analysis

A full statistical analysis plan will be finalised prior to any analyses. Statisticians from the Uppsala Clinical Research Center will oversee the statistical analyses. The primary analysis will follow the ITT principle, including all included patients in their assigned groups, regardless of protocol adherence. Additional analyses will include per-protocol analyses, that is, excluding patients with protocol violations.

Descriptive analyses of the study population will be performed, with continuous data presented as mean±SD for normally distributed variables or as median and range for non-normally distributed variables. Categorical variables will be reported as frequencies and percentages. All outcomes will be summarised by study group, overall and by ward, descriptively. Comparative statistics between study groups will be conducted, with all statistical tests being two-sided and a p value<0.05 considered statistically significant.

Models for analysing primary and secondary outcomes will include both unadjusted and fully adjusted analyses. Adjustments will account for age, gender, education level, ward type (geriatric or surgical), number of medication changes persisting post-discharge, number of medications at discharge, support by automatic dose-dispensation of medications and duration of hospitalisation. Effect estimates, including ORs, HRs and rate ratios will be presented with 95% CI and p values.

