#### Primary outcome analysis

Linear regression models with robust SEs will be used to estimate the effect of the treatment groups on the CMDD-M score. The results will be reported as effect estimates. A sensitivity analysis of the primary outcome will be performed using a permutation-based Wilcoxon non-parametric test.

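### The exploratory interrupted time series is printed with time and period only, so a step in ward mix at the switch enters its effect estimate, and for three outcomes the estimate is on a different scale from the main result

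*Protocol article*

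**What the plan says.** Under Rationale for study design, the protocol article explains that randomisation was not feasible and adds the ITS to the pre–post comparison for exploratory purposes. It says the ITS "allows for a more nuanced interpretation of the primary results by accounting for potential seasonal variations and changes in effect over time".

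Under Exploratory analyses, "A linear regression model will be estimated as follows" is followed by Y = b0 + b1T + b2I + e. T is days since study start, I marks the period, and e takes up everything else. The outcomes are the CMDD-M score, the share with the maximum CMDD-M score, the PIMCH-Q score, and "the number of non-adherence instances to medication changes persisting post-discharge and prevalence of patients who are fully adherent to medication changes". Results are reported as regression estimates.

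The main analyses of the same five outcomes are set out differently:

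- Statistical analysis: "Models for analysing primary and secondary outcomes will include both unadjusted and fully adjusted analyses". The covariate list begins "Adjustments will account for age, gender, education level, ward type (geriatric or surgical), number of medication changes persisting post-discharge" and goes on to number of medications at discharge, dose-dispensation support and length of stay.
- Primary outcome analysis, for the CMDD-M score: "Linear regression models with robust SEs will be used".
- Secondary outcome analysis: linear regression for PIMCH-Q, logistic regression with ORs for the two binary outcomes, and quasi-Poisson regression with rate ratios for the non-adherence count.

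Under Study population and recruitment, all eligible patients are invited in the control period. In the intervention period inclusion depends on pharmacist capacity and, when capacity is exceeded, on a random priority number drawn within each study ward.

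**The concern.** The ITS is the only planned analysis that models calendar time, and it is offered as help in reading the primary result of a non-randomised before–after comparison. Its natural use is to ask whether the estimated effect survives once a time trend is allowed for. That question has a clean answer only if nothing but the time term differs between the two estimates being compared.

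As printed, two other things can differ. Against the adjusted main estimate, the covariates drop out together with the addition of T. For the binary and count outcomes, the scale changes too.

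The missing covariates matter because the recruitment rule changes at the same moment as the intervention starts. Random priority within a ward protects the mix of patients inside that ward, but not the mix between wards. Each ward has one full-time-equivalent pharmacist, and recruitment stops on a total of 115 per period. If capacity binds more often on one ward than on another, the ward shares move at the switch. A time trend cannot absorb an abrupt change of that kind.

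**Working it through.** The article gives no numerical result for the ITS, so there is no figure to reproduce. Inputs from the article: 115 patients per period; about 6 months control, 2 months training and 6 months intervention; target difference 1 point; pilot SD 2.6. Assumptions: patients evenly spread over days 0–182 and 243–425; the ward difference, the shift in ward share, the intervention SD and the event rates as stated in each step.

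**1. Step in case mix.** Let W mark geriatric ward, let γ be the CMDD-M difference between ward types, and let the geriatric share change by δ at the switch with no other trend. With W omitted, the ITS estimates

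b2* = b2 + γ × δ.

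Projecting such a step on the design [1, T, I] gives a coefficient of 1.00 on I. A purely linear drift gives 0.00, because T takes it up.

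| Ward difference γ (assumed) | Share step δ (assumed) | Bias in b2 |
|---|---|---|
| 1 point | 0.10 | 0.1 |
| 1 point | 0.20 | 0.2 |
| 2 points | 0.10 | 0.2 |
| 2 points | 0.20 | 0.4 |

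The unadjusted main estimate, a plain difference in means, takes in the same γ × δ. The adjusted main estimate removes the part due to ward type.

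**2. Comparability by outcome.**

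| Outcome | Main model | ITS as printed | Same scale? |
|---|---|---|---|
| CMDD-M score | linear, points | linear, points | yes |
| PIMCH-Q score | linear, points | linear, points | yes |
| Maximum CMDD-M | logistic, OR | linear, risk difference | no |
| Fully adherent | logistic, OR | linear, risk difference | no |
| Non-adherence count | quasi-Poisson, rate ratio | linear, mean difference | no |

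The size of the scale gap, with assumed rates: a risk difference of 0.20 is an OR of (0.30/0.70)/(0.10/0.90) = 3.9 when moving from 10% to 30%, but (0.25/0.75)/(0.05/0.95) = 6.3 when moving from 5% to 25%. A rate ratio of 0.70 is a mean difference of −0.15, −0.30 or −0.60 for control means of 0.5, 1 and 2. One number cannot be read off the other without the baseline.

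**3. Standard errors.** The sample size section expects a smaller variance in the intervention period. With SD 2.6 against an assumed 1.5 and equal period lengths, the ordinary and true SEs of b2 are both 0.70 (ratio 1.00), so coverage is right. With unequal lengths, nominal 95% intervals for CMDD-M cover about 93% (6 against 4 months) to 97% (5 against 9 months).

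**4. Bias against precision.** The correlation of T and I is 0.9166, so the variance inflation is 1/(1 − 0.9166²) = 6.3. The SE of the simple contrast is 2.6 × √(2/115) = 0.34. The SE of b2 is 0.34 × √6.3 = 0.86, taking SD 2.6 in both periods. A bias of 0.1 to 0.4 is then 0.1/0.86 = 0.12 to 0.4/0.86 = 0.47 of one SE.

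**The case against.** The strongest reply is that the article is being read too literally. It never says that the ITS is unadjusted. Every ITS outcome is a primary or secondary outcome, and the general sentence on unadjusted and adjusted models could be taken to cover it. A full analysis plan is promised before any analysis. This stands in part: the reach of that sentence is uncertain. But the article prints a complete equation, defines every term, and leaves no place for covariates, so the text as fixed points the other way.

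A reader might infer that the ITS cannot be set beside the main results at all. The documents do not support that. For CMDD-M, the primary outcome, and for PIMCH-Q, the article plans an unadjusted linear main estimate, and b2 differs from it only by the time term.

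A reader might also infer that the ITS is less protected than every main analysis, or that its intervals are invalid. Neither holds. The unadjusted main estimate takes in the same step, and the ITS additionally absorbs linear drift. Robust SEs are stated only for the CMDD-M score, and their absence changes nothing with the roughly equal periods that the article expects.

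Three further points stand. The ward difference and the share step are assumptions, and within-ward random priority limits the problem mainly to the mix between wards. The bias range is less than half the SE of b2. A linear model for a yes/no outcome is a legitimate estimate of a risk difference; the wording on prevalence and regular intervals could even mean aggregated data, although T is in days and no interval is defined. Also, odds ratios are non-collapsible, so matching the logistic form does not perfectly isolate the effect of adding time.

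**Conclusion.** The point holds in a limited form. The printed ITS has no covariates, while the main analyses of the same outcomes adjust for ward type and more, and the recruitment rule changes at the very moment the ITS is meant to examine. A step in ward mix enters b2 one for one. This is 0.1 to 0.4 CMDD-M points under the assumed 1 to 2 point ward difference and 10 to 20 percentage point shift, and the unadjusted main estimate carries the same bias.

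For the two scores, b2 may be read against the unadjusted main estimate but not against the adjusted one. For the two binary outcomes and the count it is also on another scale from the ORs and rate ratios. The robust-SE part is minor. Because the analysis is exploratory and imprecise, this affects how the primary result is interpreted, not the primary test itself.

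**What to change.** In the analysis plan, before any data are analysed:

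- Fit each ITS unadjusted and also with those planned covariates that are fixed before the intervention acts: ward type at least, and also age, gender and education level.
- Use robust SEs.
- Compare b2 only with a main estimate that has the same covariates and the same scale. If the ITS uses a shorter covariate list than the fully adjusted main model, fit the main model with that list as well.
- For the binary and count outcomes, either fit the ITS as logistic and quasi-Poisson models, or keep the linear form and report the main result also as a risk or mean difference. The second route avoids the non-collapsibility of the OR.

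All of these covariates are already collected. The cost is a few sentences and slightly more analysis work. The ITS stays exploratory.

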#### Process evaluation

Quantitative data from the process evaluation will be presented with descriptive statistics by study group and in total. No formal statistical tests will be performed.

## Ethics and dissemination

This study involves human subjects and the handling of sensitive personal health data. Although there is a risk associated with collecting sensitive patient data, we will minimise these risks by adhering to the General Data Protection Regulation^56^ and the Declaration of Helsinki.^57^ All participants will provide written informed consent before participation (online supplemental file 1). The study has been approved by the Ethical Review Authority in Sweden (registration no. 2023-03518-01 and 2024-04079-02).

The aim of this intervention study is to evaluate whether a novel approach to medication-related discharge communication can improve patient care. The comparator chosen for this study is the current standard discharge process (care as usual), selected because it reflects the routine practices patients experience in the study settings and provides a relevant baseline for evaluating the intervention’s impact. During the intervention period, in addition to the usual care, the intervention focuses on enhancing the quality of medication-related communication at discharge, involving patients and/or caregivers in discussions with HCPs and offering a follow-up call after discharge to reinforce information retention. During the clinical pharmacists’ follow-up phone calls with patients in the intervention group, new issues may be identified that need attention. If the pharmacist making the call is not the appropriate person to handle these issues, they will consult with another suitable HCP to ensure the problem is addressed.

We plan to publish the results of the main trial and any substudies in international peer-reviewed open-access journals, as well as present them at national and international conferences. The trial is expected to result in multiple published manuscripts, contribute to at least one PhD thesis and support improved implementation of current Swedish regulations for medication-related discharge communication.^35^
